### Data Collection Methods & Data Management

All assessments will be conducted by research assessors who are either employed as Research Assistants by the centres involved, or are Clinical Studies Officers from the local Clinical Research Network. They will all receive training in rating the outcome measures. For the CAPS-5, this includes at least 1 day full training followed by rating a recording of an interview between an actor and an experienced interviewer. Assessors could be signed off if they score within 10% of the total score agreed by two of the authors (JB, CL), score differently on a maximum of four items and do not score more than one point different on any individual item. In order to ensure accurate ratings, assessors will receive video CAPS-5 interviews every 6 months to rate and return to JB and CL who will provide feedback.

Once they receive a referral, assessors will contact the potential participant by telephone to conduct a screening questionnaire made up of the TSQ and simple questions to assess inclusion criteria 1–3 and all of the exclusion criteria. Eligible participants will be sent a Participant Information Booklet and a daily diary and will be asked to monitor their symptoms for 2 weeks, as previous studies have found that this results in significant reduction in symptoms for some PTSD sufferers [33].

After the 2 week monitoring period, those still interested in taking part will be asked to attend a face-to-face appointment. Assessors, who have been trained in Good Clinical Practice (GCP) and receiving informed consent, will begin the consent process with the participant by reading through the Patient Information Booklet together and giving them to time to ask questions about the study. The assessor will then ask the participant to complete the triplicate study Consent Form if they are happy to do so. One copy will be given to the participant to keep. The assessor will then conduct the baseline assessment, which will assess inclusion criteria 4–6 and re-check criteria 2 (single event) and exclusion criteria 7. They will collect demographic data and the outcome measures previously outlined. Follow-up assessments will occur, as close as possible, to 16 weeks and 52 weeks post-randomisation. This will involve re-administration of the outcome measures and may be conducted face-to-face or on the telephone.

To improve data quality and completeness we have developed a study specific online database which can be accessed by all of the assessors. During the assessments, participants are encouraged to complete the self-report questionnaires directly onto the computer and assessors also complete the remaining parts of the interview online. The database flags up any missing variables, or entries outside the permissible range, thus ensuring complete and accurate data. Access to the database will be restricted to named study personnel only via a secure login and password. The system will be roles-based with restricted read/write/edit permissions. Any changes made to the data will be stored in the audit log within the system’s database with a full history of changes being recorded. The system will be accessible via any online PC, tablet or mobile device. Data will be stored securely on a secure server. In case of lack of access to an internet connection, we also have back-up paper case report forms which are entered onto the database as soon as possible. When paper copies are used, a copy will be sent to the trial co-ordinating centre and the data entered will be verified.

Qualitative interviews will be conducted with a sample of participants once they have consented to the trial but ideally prior to starting the intervention, and then again after the intervention. A sample of therapists will also be interviewed prior to commencing delivery of the interventions and again on completion. All interviews will be digitally audio-recorded then transcribed by a member of the study team.

To aid retention, participants will be offered a £10 shopping voucher on completion of the 16 week and 52 week follow-up assessments as a token of appreciation for their participation in the study. Where a participant wishes to withdraw from the intervention, their participation in the follow-up assessments will be encouraged. Unless a participant has withdrawn consent for follow-up, repeated attempts using different approaches will be made to contact participants who cannot be easily contacted. In a step-wise manner, this will involve checking contact details with their study therapist, calling the individual on all contact numbers provided on various days of the week and at different times, sending emails and a letter to the addresses provided. If contact can still not be made, the individual’s GP will be contacted to check contact details are correct. If these attempts do not result in contact being made within 1 month of loss of contact or the planned follow-up, a letter will be sent asking the participant to re-establish contact if they are able to and advising that they will be contacted again at the next follow-up point unless they advise otherwise. For any participant reluctant to complete the full outcome assessment at follow-up we will attempt to gain the CAPS-5 information as a minimum dataset. As much information as possible will be collected from protocol non-adherers, with a minimum of the primary and secondary outcome measures and reasons for non-adherence.

### Statistical methods

The primary analysis will be performed using analysis of covariance, predicting follow-up CAPS-5 score controlling for baseline CAPS-5 score and important patient characteristics (including all minimisation variables). This will be a complete case intention to treat analysis. Checks will be made to ensure there is no appreciable clustering of outcomes within therapists, but if such clustering exists the primary analysis will be hierarchical. The results will be summarised using point estimates, 95% confidence intervals and *p*-values. Since this is a non-inferiority design, we will be checking whether the confidence interval for the difference between arms lies entirely within the 5 point non-inferiority margin. Participants with missing CAPS-5 score at follow-up will have a CAPS-5 score estimated from available IES-R scores (this will involve building a prediction model using information from participants with both IES-R and CAPS-5 scores). We will explore differences in treatment effects by gender in a sub-group analysis by including an interaction term between treatment arm and gender.

A sensitivity analysis will use multiple imputation to account for missing data if the number of cases lost due to incomplete information exceeds 10%. Secondary outcomes include: CAPS-5 at 52 weeks, IES-R, WSAS, PHQ-9, GAD-7, AUDIT-O, MSPSS, EQ-5D, ISI, GSES, PTCI, adapted CSSRI-EU and CSQ-8. These are all continuous measures and will be analysed similarly to the primary outcome. Transformations will be explored to improve model fit if distributional assumptions are not satisfied. This will be assessed by visual inspection and formal fit statistics compared to decide on the transformation chosen.

IES-R scores over time will be explored using a hierarchical modelling (including clustering by therapist if this is identified in the primary analysis) and an appropriate covariance structure allowing for IES-R scores within an individual to be correlated over time. Covariance structures to be explored include autoregressive terms (AR), moving average (MA), and combined terms (ARMA). This will facilitate the fitting of IES-R trajectories over time (since randomisation) interacted with intervention arm, whilst also controlling for the same covariates as the primary analysis. A sensitivity analysis will use multiple imputation to account for missing data if the number of cases lost due to incomplete information exceeds 10%. A further sensitivity analysis will account for patient adherence to the protocol using complier adjusted causal effect (CACE) analysis [57]. All analyses will be performed in the R programming language and environment or SPSS [58, 59].

Qualitative data will be analysed using framework analysis [60]. This is a systematic five-stage method, which is increasingly being used in health care research [61]. It will allow us to compare themes across time point, treatment centre, and interviewee category (i.e. patient and therapist). We will identify contradictory data, as points of contrast as well as similarities will be important in order to understand uptake of the GSH tool. The method is well defined and allows for greater transparency. Vital measures will be put into place to ensure validity and reliability. More than one person will be involved in the analysis and double coding will be carried out until consensus is reached. The framework analytic approach has been selected as it is a recognised transparent analytic approach. This qualitative component has been designed using the principles of the Critical Appraisal Skills Programme qualitative checklist, to ensure the quality of qualitative research [62].

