#### Spring: An internet based guided self-help Programme for PTSD

Spring is an online GSH programme based on TFCBT. It uses the same principles as TFCBT but aims to reduce contact time with the therapist by providing some of the therapy content and activities in an accessible self-help format. Potential advantages include that the service user can engage in the intervention at a time and place convenient to them which may reduce drop out, and it may also reduce waiting list times as it should reduce the input time required for therapist.

The expectation is that Spring will be delivered by the same therapists delivering the TFCBT. All the therapists will receive a half day’s training from two of the authors who were involved in developing the intervention and delivering it in the pilot study (NK, NR). Therapists also receive ongoing supervision of one or more training cases until they are regarded as competent. The therapists will work from a manual and, for the duration of the trial, will receive supervision once per month from NK or NR.

Spring is an 8 week online program comprising eight steps (see Table 2. Spring PTSD Steps).

**Table 2 Tab2:** Spring PTSD Steps

Step 1: Learning About My PTSD – Psychoeducation about PTSD illustrated by four actors describing their experience of PTSD to different types of traumatic event.
Step 2: Grounding Myself - Explanation of grounding and its uses along with descriptions and demonstrations of grounding exercises.
Step 3: Managing My Anxiety – Education about relaxation techniques with learning through videos of a controlled breathing technique, deep muscular relaxation and relaxation through imagery.
Step 4: Reclaiming My Life – Behavioural re-activation to help individuals return to previously undertaken/new activities.
Step 5: Coming to Terms with My Trauma – Provides rationale for imaginal exposure, narratives of the four video characters. The therapist helps the participant to begin writing a narrative, which they complete remotely and read every day for at least 30 min.
Step 6: Changing My Thoughts – Cognitive techniques to address PTSD symptoms.
Step 7: Overcoming My Avoidance – Graded real life exposure work.
Step 8: Keeping Myself Well – This session reinforces what has been learnt during the programme, provides relapse prevention measures and guidance on what to do if symptoms return.

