### Sample size

As the study aims to demonstrate non-inferiority of GSH for PTSD compared to TFCBT, the power calculation considers the non-inferiority margin as opposed to the effect size. The non-inferiority margin will be 5 points on the 80 point CAPS-5 scale. A recent meta-analysis [11] indicates that the standardised mean difference between TFCBT and waitlist/usual care for the treatment of PTSD is − 1.62. This corresponds to 16.6 points on the CAPS-5. This means that if we demonstrate non-inferiority to within 5 points of the gold standard, we will also demonstrate superiority over wait list/usual care in line with International Conference on Harmonisation Harmonised Tripartite Guideline (Statistical Principles for Clinical Trials) E9 (ICH E9) guidance for non-inferiority studies [53, 54].

Pilot work indicates an intraclass correlation coefficient of 5.6% at the therapist level at 10 weeks. At 22 weeks, however, there was no observable clustering of CAPS-5 scores amongst therapists. Given our primary outcome (CAPS-5) is measured at 16 weeks we have allowed for 1% clustering and recalculated the sample size. We have allowed for 20% attrition. On the basis of the anticipated average therapist cluster size being four, the design effect is 1.03, requiring a 3% inflation of the sample size. This results in a final sample size of 192 (inflated from 186) which provides 90% power (nQuery v7.0).

For the qualitative elements of the study, the sample size will be guided by preliminary analysis and constant comparison (comparing and contrasting themes from other interviews) during each data collection phase, until the research team is satisfied that there is data saturation and no new themes which are important to the research question arise [55]. However, it is helpful to have a guide to sample size for study planning. Based on previous research [56] we propose that interviews will be conducted with 10–20 participants and 8 therapists purposefully sampled from the different geographical sites.

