### Allocation and blinding

Where possible, baseline measures will be collected electronically using an online database. Following completion of the baseline assessment, the database will inform the assessor that the participant is eligible for randomisation and the assessor will click the ‘Randomise Participant’ button. The database will allocate the participant to either GSH or TFCBT using pre-programmed software. This information will not be available to the assessor, who is blind to allocation, instead the database will email the trial manager who will inform the appropriate therapist. Individual randomisation will be conducted using an online minimisation algorithm generated by the trial statistician. The ratio will be 1:1. Minimisation will ensure balance between trial arms for gender, but will retain a random element and will be stratified by research centre.

It is not possible to blind the therapists or the participants given the complex interventions under investigation. However, the outcome assessors will be blind to treatment allocation and the therapists and participants will be asked not to discuss their allocation with the assessor. This will be stressed at the start of the interview and will minimise any potential bias the assessor may have when conducting the outcome assessments. To measure the success or otherwise of allocation concealment, the assessors will be asked to guess the participant’s allocation before and after each assessment. This will be recorded and compared to chance at the end of the study.

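### The primary model is chosen by a check of the outcome data that cannot tell the planned therapist ICC of 1% from zero; the therapist term should be fitted unconditionally

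*Protocol article*

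**What the plan says.** Under Statistical methods, the primary analysis is an ANCOVA of follow-up CAPS-5 on baseline CAPS-5 and patient characteristics, including all minimisation variables. The therapist enters only by way of a check: "Checks will be made to ensure there is no appreciable clustering of outcomes within therapists", and "if such clustering exists the primary analysis will be hierarchical". The same section makes therapist clustering in the IES-R model conditional on its having been found in the primary analysis. Non-inferiority is judged by whether the 95% confidence interval respects the 5-point margin.

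Under Sample size, clustering is assumed. The pilot evidence is mixed: "Pilot work indicates an intraclass correlation coefficient of 5.6% at the therapist level at 10 weeks", but "At 22 weeks, however, there was no observable clustering of CAPS-5 scores amongst therapists". For the 16-week endpoint, "we have allowed for 1% clustering and recalculated the sample size". The resulting inflation is stated: "On the basis of the anticipated average therapist cluster size being four, the design effect is 1.03", which takes 186 to 192.

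Two further statements bear on the point. On who treats whom: "The expectation is that Spring will be delivered by the same therapists delivering the TFCBT". On allocation, minimisation balances gender and "will be stratified by research centre".

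**The concern.** The sample size pays for therapist clustering, while the analysis leaves it out unless the trial's own data show it. That has two consequences.

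First, the check has to find a small variance component with about four participants per therapist. If it cannot separate the planned ICC from zero, its result is close to noise, and so is the choice of primary model that follows from it.

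Secondly, the trial is decided by one confidence limit against 5 points. Two candidate primary models, selected after outcome data are seen, leave a choice at the place where the conclusion turns. The stated rule has this property whatever cut-off a SAP may attach to it.

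**Working it through.** **Inputs.** From Sample size: ICC 1% (planned), 5.6% (pilot, 10 weeks), none observed (pilot, 22 weeks); average therapist cluster 4; attrition 20%; N = 192. The number of therapists is not given. Assumptions: 192/4 = 48, or 153.6/4 = 38.4, with 20 as a sensitivity case. The number analysed is 192 × 0.8 = 153.6, which is 3.2, 4 and 7.7 per therapist respectively.

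**The plan's own figure.** Design effect = 1 + (4 − 1) × 0.01 = 1.03, and 186 × 1.03 = 191.6, so 192. It reproduces.

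**Can the check see the clustering?** The article does not name the form of the check, so two forms are tried. For k therapists with m analysed each, the between/within variance ratio F satisfies F × (1 − ρ)/(1 + (m − 1)ρ) ~ F(k − 1, k(m − 1) − 3), where 3 degrees of freedom are taken for covariates.

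Example with k = 48, m = 3.2, ρ = 0.01: the 5% critical value is 1.484 on 47 and 102.6 df, the factor is 0.99/1.022 = 0.969, and the probability of exceedance is 0.065. An estimated ICC above zero corresponds to F > 1.

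| Therapists × analysed each | 5% test, ICC 1% | 5% test, ICC 5.6% | Estimated ICC > 0, true ICC 0 | Estimated ICC > 0, true ICC 1% |
|---|---|---|---|---|
| 48 × 3.2 | 0.065 | 0.177 | 0.488 | 0.538 |
| 38.4 × 4 | 0.068 | 0.208 | 0.482 | 0.541 |
| 20 × 7.7 | 0.080 | 0.316 | 0.465 | 0.550 |

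Simulation of a REML likelihood-ratio test for a random therapist intercept (154 patients; 38 or 48 therapists; balanced and unbalanced) gave 0.064–0.073 at ICC 1%, 0.170–0.259 at 5.6% and 0.041–0.050 with no clustering. Neither form separates 1% from zero.

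**What does ignoring therapists cost?** If the true variance of the arm difference is DE times what plain ANCOVA assumes, the one-sided error of a nominal 2.5% limit is 1 − Φ(1.96/√DE). DE depends on how therapists relate to arms.

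| Design | DE at 1% | Error | DE at 5.6% | Error |
|---|---|---|---|---|
| Both arms, common therapist effect: DE = 1 − ρ | 0.99 | 0.0244 | 0.944 | 0.0218 |
| Both arms, effects independent by arm, 1.6 per therapist and arm | 1.006 | 0.0253 | 1.034 | 0.0269 |
| As above, 2 per therapist and arm | 1.01 | 0.0256 | 1.056 | 0.0282 |
| Therapists nested in arm, 3.2 each | 1.022 | 0.0263 | 1.123 | 0.0322 |
| Therapists nested in arm, 4 each | 1.03 | 0.0267 | 1.168 | 0.0349 |

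Example (nested, 4 each, 5.6%): √1.168 = 1.081, 1.96/1.081 = 1.81, upper tail 0.0349. The nested rows are the worst case and not the expected design. The first row assumes an even split of each therapist's patients between arms.

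**The case against.** The strongest reply is that the numerical harm is negligible in the design the protocol expects. With the same therapists in both arms and a common therapist effect, plain ANCOVA errs on the safe side. The 5.6% comes from 10 weeks, and no clustering was seen at 22 weeks. At the planned 1%, even the worst case moves 2.5% only to 2.67%. All of this stands.

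A reader might go further than the documents allow in three ways.

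- *The check will almost never find clustering, so the trial will usually ignore it.* That holds only if the check is a 5% significance test. The article names no test, and under a rule of estimated ICC above zero the hierarchical model would be chosen in about half of trials. The missing threshold may be in the SAP and is not itself the finding.
- *Intervals will be too narrow whenever clustering is real.* Not with crossed therapists and a common effect. The 3.5% figure needs therapists nested in arm with four each.
- *Research centre has been left out of the model.* The article describes one minimisation procedure with gender and centre, and adjusts for all minimisation variables, so centre is reasonably covered. The wording is at most ambiguous.

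It can also be said that a random-intercept model with a zero variance estimate returns the ANCOVA, so the data still shape the fit; at ICC 1% the table implies a zero estimate in about 45% of trials. That is true, but it is then the output of one pre-specified estimator and not a choice between models.

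What the reply does not remove: crossing is stated only as an expectation, the Challenges section anticipates therapists leaving, and allocation is not described as balanced by therapist. With about four patients each, uneven splits are likely, and a check of overall clustering does not address therapist effects that differ by arm.

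**Conclusion.** The point holds as one of pre-specification, with a small numerical effect. The rule selects the primary model from the outcome data by a check that, under both forms examined and for 20 to 48 therapists (an assumption), cannot distinguish the ICC the trial was sized for from none. One-sided error from ignoring therapists lies between 0.0218 and 0.0282 if therapists treat both arms, and reaches 0.0349 only with therapists nested in arm at ICC 5.6%. The documents do not support a claim that the planned analysis is materially anti-conservative. They do support removing a data-driven choice from a decision that rests on one confidence limit, in an analysis that should match its own sample-size assumption.

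**What to change.** Make the model with a random therapist intercept the primary analysis regardless of any check, with fixed effects for arm, baseline CAPS-5, gender and research centre (named explicitly) and small-sample degrees of freedom. Report plain ANCOVA, and a model that lets the arm difference vary by therapist, as sensitivity analyses. The second should not be primary, because about 1.6 analysed patients per therapist and arm estimate that variance poorly. Remove the same condition from the IES-R model.

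The cost is a change of wording before outcome data are seen. N stays at 192, since the design effect of 1.03 is already included. If there is no clustering, the loss of precision is very small.

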The therapist initially meets with the participant at the service base for an hour to develop a rapport, learn about the participant’s trauma and describe the programme, which the participant then completes online in their own time. There are four subsequent fortnightly meetings of 30 min, normally undertaken face-to-face, but potentially deliverable via the internet or telephone, according to participant preference. The participant will also receive four brief telephone calls or email contact between sessions to discuss progress, identify any problems that have arisen and sometimes set new goals. The modules are accompanied by homework. At each session, the therapist reviews progress by logging into a clinician dashboard, and guides the participant through the programme. The aim of the guidance is to offer continued support, monitoring, motivation and problem solving. The eight online steps are usually completed in turn with some later steps relying on mastery of techniques taught in earlier steps. Each step provides psycho-education and the rationale for specific components of treatment. Each step activates a tool that becomes live in the Toolkit area of the website and aims to reduce traumatic stress symptoms. Everything entered into the Toolkit becomes visible (with the participant’s knowledge) to the therapist via the dashboard to facilitate input. The programme can be accessed online via a web browser or through an App. Participants will be able to use their PCs, tablets or smart phones to engage with the programme. A screenshot taken from Step 1 can be seen in Fig. 1: Spring Screenshot. Participants will be asked to complete the IES-R at each face-to-face session to measure and monitor their PTSD symptoms.

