Additional, non-IAPT measures will be administered at 16 and 52 weeks post-randomisation. Perceived social support will be measured using the Multidimensional Scale for Perceived Social Support [45], and the level of healthcare resource utilisation for health economic analysis will be determined by an amended version of the Client Socio-Demographic and Service Receipt Inventory European Version [46]. Changes in health related quality of life will be measured by the EQ-5D [47] and changes in sleep measured by the Insomnia Severity Index [48]. A short version of the Post-Traumatic Cognitions Inventory [49] and the General Self Efficacy Scale [50] will be collected to determine effects on cognitions and self-efficacy respectively. The Client Satisfaction Questionnaire [51] will be collected at 16 weeks post-randomisation only, to evaluate treatment satisfaction.

The IES-R will be collected at each therapy contact to provide clinical feedback and also to facilitate imputation for missing data, if required. How frequently it is collected will depend on the frequency of therapist contact, but is likely to be weekly in the TFCBT arm and fortnightly in the GSH arm.

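### The primary analysis is called complete case, yet missing CAPS-5 scores are to be predicted from IES-R; if each prediction is analysed as observed, the 95% CI is too narrow

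*Protocol article*

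**What the plan says.** All places are in the protocol article.

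- **Statistical methods, analysis set.** The primary model is an ANCOVA of follow-up CAPS-5 on baseline CAPS-5 and patient characteristics. "This will be a complete case intention to treat analysis".
- **Statistical methods, same paragraph, after the decision rule.** "Participants with missing CAPS-5 score at follow-up will have a CAPS-5 score estimated from available IES-R scores", and "this will involve building a prediction model using information from participants with both IES-R and CAPS-5 scores". The sentence carries no condition and is not labelled a sensitivity analysis.
- **Statistical methods, next paragraph.** "A sensitivity analysis will use multiple imputation to account for missing data if the number of cases lost due to incomplete information exceeds 10" per cent.
- **Outcomes.** IES-R is collected at every therapy contact for clinical feedback and "also to facilitate imputation for missing data, if required". Its frequency "is likely to be weekly in the TFCBT arm and fortnightly in the GSH arm".
- **Spring section (the GSH arm).** "Participants will be asked to complete the IES-R at each face-to-face session". The same section allows the fortnightly meetings to take place by internet or telephone.
- **Sample size.** "We have allowed for 20% attrition". The margin is 5 points and the total is 192.

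**The concern.** A complete case analysis leaves out anyone without the outcome. Giving those people a predicted outcome puts them back in. The paragraph does both and does not say which data set is compared with the margin.

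The second problem follows from the prediction. A regression prediction lies on the fitted line and has none of the scatter that real scores have around it. If one such value per person enters the ANCOVA as an observation, the residual variance is too small and the sample size is counted as larger than the information supports. Both effects shorten the confidence interval. The trial's conclusion rests on one confidence limit against 5 points, so an interval that is too short raises the chance of declaring GSH non-inferior when it is not. Leaving both handlings open also allows the choice to be made after the results are known.

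**Working it through.** **1. The plan's own figures.** The design effect is 1 + (4 − 1) × 0.01 = 1.03, and 186 × 1.03 = 191.6, so 192 reproduces. With 20% attrition, 192 × 0.8 = 153.6, about 154 observed cases. If everyone missing has a usable IES-R score, filling them in gives up to 192.

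**2. Inputs.** From the documents: 20% missing (the attrition allowance), the 5-point margin, and a 95% CI, which means a one-sided error of 2.5% at the margin. Assumed, because the documents do not give it: the correlation r between CAPS-5 and the IES-R predictor, taken as 0.5 to 0.8. Missingness is assumed to be completely at random.

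**3. Closed form, arm in the prediction model.** Let p be the proportion missing. Relative to the SE from complete data on everyone:

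- SE reported from the filled-in data: √[1 − p(1 − r²)]
- true SE of the estimate: √[1 + p(1 − r²)/(1 − p)]
- one-sided error at the margin: 1 − Φ(1.96 × reported/true)

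Example with p = 0.2 and r = 0.7: reported √(1 − 0.2 × 0.51) = 0.948; true √(1 + 0.25 × 0.51) = 1.062; ratio 0.892; error 1 − Φ(1.749) = 4.0%. The SD cancels.

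| p | r | reported | true | ratio | error |
|---|---|---|---|---|---|
| 0.2 | 0.5 | 0.922 | 1.090 | 0.846 | 4.9% |
| 0.2 | 0.7 | 0.948 | 1.062 | 0.892 | 4.0% |
| 0.2 | 0.8 | 0.963 | 1.044 | 0.923 | 3.5% |
| 0.1 | 0.5 | 0.962 | 1.041 | 0.924 | 3.5% |
| 0.1 | 0.7 | 0.974 | 1.028 | 0.948 | 3.2% |
| 0.1 | 0.8 | 0.982 | 1.020 | 0.963 | 3.0% |

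**4. Simulation check.** 96 per arm, implied SD 16.6/1.62 = 10.25, true difference 5, ANCOVA with baseline, arm in the prediction model, 4,000 runs per setting (Monte Carlo error about 0.3 percentage points).

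| p | r | SE ratio | 95% CI coverage | error, predicted scores | error, observed cases only |
|---|---|---|---|---|---|
| 0.2 | 0.5 | 0.849 | 90.7% | 4.6% | 2.5% |
| 0.2 | 0.7 | 0.896 | 91.9% | 4.0% | 2.6% |
| 0.2 | 0.8 | 0.919 | 93.3% | 3.3% | 2.3% |
| 0.1 | 0.5 | 0.915 | 92.5% | 3.6% | 2.5% |
| 0.1 | 0.7 | 0.945 | 93.7% | 3.0% | 2.3% |
| 0.1 | 0.8 | 0.970 | 94.3% | 3.0% | 2.8% |

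In points, at p = 0.2 and r = 0.7, the reported SE is 1.297 and the true SE 1.448. The half-width is 1.96 × 1.297 = 2.54 where 1.96 × 1.448 = 2.84 is needed, so the upper limit sits about 0.3 points too low. At r = 0.9 the effect is small (error about 3.0% with arm in the model).

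**5. Arm left out of the prediction model.** In the same runs with 20% missing and r = 0.5 to 0.8, a true difference of 5 was estimated as about 4.3 to 4.7, and the error was 7.6% to 4.7%. The plan does not state this choice, so these figures are not part of the finding.

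**6. Timing of IES-R.** GSH lasts 8 weeks; TFCBT runs for up to 12 sessions, likely weekly. For someone who misses the 16-week visit, the last session score will tend to be older in GSH: roughly 16 − 8 = 8 weeks old, against roughly 16 − 12 = 4 weeks for a full weekly TFCBT course. This can push the estimate either way. At r = 0.7 and 20% missing, with GSH IES-R scores shifted worse by an assumed 3 to 8 CAPS-equivalent points, the error was 2.8% down to 1.2% with arm in the model. If instead IES-R carries only half of the arm difference, it was 6.8%.

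**The case against.** The paragraph can be read as a sequence: estimate CAPS-5 from IES-R where possible, analyse everyone who is then complete, and turn to multiple imputation if more than 10% are still lost. It can also be read as an observed-case primary analysis with the IES-R estimate as support. Neither reading rescues the text. Under the sequence, the analysis is not complete case in the usual sense and the narrow interval applies in full. Under the other, a sentence with no condition and no sensitivity label has to be ignored.

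The words single and regression do not appear in the plan, and the content of the prediction model may properly be left to the analysis plan. That stands, which is why the size is conditional on one predicted value per person. This remains the natural reading, because multiple imputation is introduced separately and only as a sensitivity analysis.

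The size may be smaller than the 20% scenario. Early withdrawers may have no session IES-R, and follow-up puts CAPS-5 first. If only half of the 20% can be predicted, the error at r = 0.7 with arm in the model is about 3.3%. This also stands. At 20% missing the multiple imputation check would normally run, but the plan does not say whether people with a predicted score count as lost for its trigger, and that check does not decide the primary result.

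A reader might infer that the whole scheme pulls the arms together and so favours GSH. The documents do not support that: the pull depends on leaving arm out of a model that is not described, and older GSH scores, if symptoms fall during therapy, would count against GSH. A reader might also infer that GSH scores are taken only at face-to-face meetings. The Spring section does not say only; it is simply not aligned with Outcomes.

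**Conclusion.** The point holds in two parts. The definition of the primary data set contradicts itself, whatever the analysis plan adds: about 154 or up to 192 participants at the planned attrition. If one predicted score per person is analysed as observed, the 95% CI is too narrow. With arm in the model and r between 0.5 and 0.8, the SE is about 8% to 15% too small at 20% missing, and false non-inferiority is about 3.3% to 5% instead of 2.5%. At 10% missing it is about 3% to 3.5%.

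The effect is moderate. It rests on an assumed correlation, on missingness unrelated to outcome, and on everyone missing having a usable IES-R score. What is established is an interval that is too short; a net bias of the estimate in favour of non-inferiority is not. An analysis of observed cases only kept its error at about 2% to 3% in the same runs.

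**What to change.** - Name one primary handling in Statistical methods. Either use observed cases only in the ANCOVA, or use multiple imputation with arm, baseline CAPS-5 and IES-R scores with their timing in the model, pooled by Rubin's rules.
- Run the other as a sensitivity analysis whatever the percentage missing, so that the 10% trigger and the question of who counts as lost fall away.
- Remove the single predicted score from the primary decision.
- Reconcile the Spring section with Outcomes on when IES-R is collected in the GSH arm.

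The cost is a few sentences in the protocol and analysis plan, a little programming, and a slightly wider confidence interval.
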